### Intervention

The intervention consists of a respiratory muscle-strengthening exercise, by using the threshold RMT method
[54]. A training stimulus is given by asking participants to breathe repeatedly in (inspiratory muscle training) or out (expiratory muscle training) through a commercially available hand-held resistance device (Threshold IMT, Threshold PEP; Respironics, Parsippany, NJ, USA). Participants are asked to train daily over a 4-week period. Every day, participants perform five sets of 10 breaths with the device, with resting periods of 1 minute between sets. The training resistance is set at 50% of the individual’s maximum mouth pressure (maximum inspiratory mouth pressure for the inspiratory training group, maximum expiratory mouth pressure for the expiratory training group). Maximum mouth pressures are reassessed weekly, and the training resistance readjusted accordingly. Participants in the sham training group are also given a training device, with the resistance set to an ineffectual 10% of maximum mouth pressure.

Participants are instructed in the correct training technique by the investigator during the baseline session, and training technique is reviewed weekly. To document concordance with training, participants keep a training diary, noting the frequency of training and any problems encountered.

### Study parameters

Additional file
1 gives an overview of the data collected at the respective time points. Peak expiratory cough flow (PECF) of voluntary cough at the end of the intervention period (day 29) is taken as the primary study outcome. This is in keeping with the clinical scenario of aspiration and resulting pneumonia. PECF is the parameter that indicates the speed of the air expelled from the lungs during the expulsion phase of cough. Voluntary cough PECF therefore reflects a person’s capacity to move aspirated particles from the lower airway back above the vocal cords and into the pharynx through a voluntary cough maneuver
[55]. Secondary study outcomes are incidence of pneumonia, maximum mouth pressures, and peak expiratory cough flow of reflex cough at day 29.

Participants’ age, height, and weight at the time of hospital admission are recorded from clinical records.

Swallow safety is determined from the clinical swallow assessment, conducted routinely for patients admitted with acute stroke. This entails a swallow screen administered by a trained nurse. The swallow screen is conducted according to a clinical algorithm and includes observation of alertness, oro-motor function, and swallowing function. If concerns are raised, the medical team and the speech and language therapist are alerted. A clinical swallow examination by a speech and language therapist is performed, and swallow-management strategies are implemented. In specific cases, an instrumental assessment of swallowing function is performed.

For the purpose of the present study, the swallow is deemed unsafe if any precautionary instructions are issued for the participant, such as nil by mouth, recommendations of modified food textures, or specific swallowing techniques. The swallow is deemed safe, if the participant is allowed to swallow normal fluids and a normal diet without any explicit precautionary instructions.

The presence of pneumonia is determined from clinical records, from communication with the medical team, and from the participant directly.

The Nottingham Extended ADL Scale
[56], a self-reported questionnaire, is used to assess participants’ functional independence in activities of daily living (ADLs).

All respiratory testing is conducted with the participant seated comfortably, or positioned sitting up in the hospital bed. Forced spirometry (forced expiratory volume at 1 second (FEV1), forced vital capacity (FVC), and peak expiratory flow (PEF)), is conducted according to international clinical standards
[57], by using a portable spirometer (SpiroUSB; CareFusion, San Diego, CA, USA) and a bacterial filter (Spiroguard Standard; Air Safety Medical, Morecambe, England). A flanged mouthpiece (Rubber Flanged Mouthpiece MTH6400; CareFusion) is used to create an optimal mouth seal in the presence of orofacial weakness. Forced spirometry provides an assessment of participants’ lung function, and in particular of airway obstruction and restriction.

Respiratory muscle strength is assessed through measurement of maximum expiratory mouth pressure (MEP) and maximum inspiratory mouth pressure (MIP), according to international clinical standards
[58]. A portable clinical device (MicroRPM; CareFusion) is used with a bacterial filter (Mouth Pressure Bacterial Filters FIL6050; CareFusion) and a flanged mouth piece (Rubber Flanged Mouthpiece MTH6400; CareFusion).

Cough flow measurements are conducted with a calibrated pneumotachograph system
[59]. An on-site and an off-site measurement system are used. The on-site system is used for measurements at the primary study site. The off-site system is used for measurements outside the primary study site, for example at the neighboring stroke-rehabilitation unit or at participants’ homes. The on-site system consists of a Fleisch-type pneumotachograph (ID 4 cm, length 6 cm; PK Morgan Ltd, Rainham, England) connected to a face mask (Adult Face Mask, 8940 Series; Hans Rudolph Inc., Kansas City, MO, USA); a differential pressure transducer (MP45-14-871, range ± 2 cmH_2_O; Validyne Engineering, Northridge, CA, USA); a demodulator (CD15; Validyne Engineering); an analog-to-digital converter (PowerLab/16SP; ADInstruments Ltd, Oxford, England); and a laptop running LabChart data-acquisition software (LabChart Pro, version 7.2.2; ADInstruments Ltd).

For the off-site system, a different analog-to-digital converter (NI BNC-2110; National Instruments, Newbury, England) and laptop with data-acquisition software (LabView, version 5.1, National Instruments) are used. The on-site and off-site systems have the same performance characteristics: linear response from zero to 700 L/min in both directions of flow; frequency response of >20 Hz; and analog-to-digital sampling of 2 kHz. The systems are calibrated before each testing session by two-point calibration with a rotameter (InFlux OF1”S, 60 to 600 L/min flow; Techniquip Ltd, Taunton, England) at a reference flow of 500 L/min.

Voluntary and reflex coughs are assessed. For voluntary coughs, participants make repeated maximal cough efforts into a tight-fitting face mask, until five coughs of similar PECF are recorded. To elicit reflex coughs, escalating concentrations of capsaicin (0.49 to 1,000 μ*M*) are nebulized (UltraNeb U3000; DeVilbiss Healthcare Ltd, Tipton, England) and introduced into the face mask for 1 minute at a time, until the threshold is reached at which five bouts of reflex coughing are triggered. From the recorded cough-flow traces, the following parameters are derived for the five voluntary and five reflex coughs with the highest peak expiratory flow rates: peak expiratory cough flow (PECF), peak inspiratory cough flow (PICF), volume expired (VE), volume inspired (VI), glottis compression time, and cough-volume acceleration.

To monitor the safety of the intervention, blood pressure, heart rate, and blood oxygen saturation are measured before and after participants carry out RMT. Measurements are made by using a digital blood pressure monitor (UA-767 Plus; A&D Instruments Ltd, Abingdon, Oxon, UK) and a finger pulse oximeter (Onyx 9500; Nonin Medical Inc, Plymouth, MN, USA). In addition, the investigator notes any subjective discomfort reported during training. Adverse events are noted and reviewed throughout the duration of the study.

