## Methods/design

### Study design

The study is a pilot study, designed as a single-blind randomized controlled trial with three study groups. Participants are randomized to receive inspiratory muscle training, expiratory muscle training, or sham RMT. After the baseline assessment, participants undergo a 4-week intervention period. Weekly investigator visits are conducted during the intervention period. The primary study end point is at the end of the intervention period (day 29). A final reassessment is conducted at 12 weeks after baseline. One investigator conducts all study procedures, including screening for eligibility, gaining consent, conducting study assessments, and introducing and assisting with the intervention. A summary of the study timeline and all data collected is given in Additional file
1. The participant flow through the study is described in Figure 
1.

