### Randomization, blinding, and treatment allocation

Sequentially numbered sealed envelopes containing the treatment allocation were prepared by a researcher unrelated to the study team. The randomization sequence was computer-generated. Block randomization (blocks of 12, containing four participants per study arm) was used to ensure even participant spread across the trial groups.

For each participant, the investigator opens the respective envelope after informed consent has been gained and immediately before conducting the study baseline session. Thereafter, the investigator is aware of the participant’s group allocation. Participants, caregivers, and healthcare professionals are unaware of group allocation throughout the study period.

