### Statistical analysis

Descriptive statistics will be used to present group characteristics at baseline; to compare study completers with participants who discontinued the study; and to compare participants with good training completion with those with poor training concordance. Training-safety data will be summarized descriptively and compared against pre-set safety parameters (standard safe ranges of vital parameters as used in clinical practice).

Inferential statistics will be used to evaluate the effect of treatment on the primary and secondary outcome parameters. The hypotheses under investigation are as follows: RMT (inspiratory or expiratory) is effective for improving voluntary cough effectiveness (voluntary cough PECF); RMT (inspiratory or expiratory) is effective for improving reflex cough effectiveness (reflex cough PECF); expiratory muscle training is effective for improving expiratory muscle strength (MEP); inspiratory muscle training is effective for improving inspiratory muscle strength (MIP); RMT (inspiratory or expiratory) is effective for reducing the incidence of pneumonia.

The sample-size calculation followed an ANOVA model of inferential statistical analysis. However, it is anticipated that the study sample will show considerable heterogeneity, in which case, an analysis of covariance (ANCOVA) model is more powerful in detecting a difference in study arms
[62]. ANCOVA will be used to compare group means of voluntary and reflex cough PECF, MEP, and MIP at the primary end point (day 29). The following covariates will be adjusted for: gender, age, smoking, stroke severity (NIHSS score), training intensity, and a predictor variable for “missingness”, which will be determined through logistic regression. Fisher Exact test will be used to compare the incidence of pneumonia from baseline through week 4 between the three study groups. Adjustments for multiple testing will be made by using the Benjamini-Hochberg method
[63].

Four approaches to dealing with missing values will be compared in a sensitivity analysis: intention-to-treat analysis, substituting missing values through predictive model-based imputation
[64]; intention-to-treat analysis, substituting missing values through propensity score imputation
[65]; intention-to-treat analysis, substituting missing values with baseline data; and complete case analysis, using only data from participants who completed the primary end point.

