### Weaknesses

The methods for identifying the presence of swallowing difficulty and pneumonia in the current study may be regarded as a limitation. To minimize participant burden created by additional medical procedures, it was decided to take a pragmatic approach and observe clinical and self-reported information on swallowing function and pneumonia. A more-detailed instrumental assessment of swallowing, such as video-fluoroscopic examination of swallow, could be used to determine the degree of dysphagia and aspiration. Objective diagnostic criteria for pneumonia, including assessments of chest radiographs and blood results
[69,70], could be used to support the detection of pneumonia.

A further limitation to the study is the lack of investigator blinding. The investigator is masked to treatment-allocation sequence, but is aware of group allocation from the point of randomization.

Although the clinical purpose of this research is to reduce the risk of pneumonia after stroke, the study uses voluntary cough flow as a surrogate primary outcome. This surrogate outcome was selected to minimize the required sample size. Designing the study according to the primary outcome, pneumonia, would require a considerably larger sample. For example, it could be assumed that both intervention groups would show a reduction in pneumonia rates from 15% to 7.5% compared with the control group. To give 80% power at the 5% significance level, this would require approximately 180 participants per group (using the χ^2^ test and not accounting for attrition).

The choice of voluntary cough flow as a surrogate primary outcome in this study was based on the physiological rationale to the research. Also, good evidence shows that reduced voluntary cough flow in stroke patients is associated with higher risk of aspiration, and therefore aspiration pneumonia
[35,36]. To our knowledge, the direct relation between voluntary cough flow and pneumonia has not been investigated in stroke populations. The importance of cough flow may be inferred from populations with neuromuscular conditions, where reduced levels of voluntary cough flow indicate the need for assisted airway clearance

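### Pneumonia is read from three unranked sources by the one investigator who knows the allocation; with so few events, about three reconciling decisions in one direction could decide the planned test

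*Protocol article*

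**What the plan says.** Four places in the protocol article bear on this.

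- **Study parameters** gives the sources: "The presence of pneumonia is determined from clinical records, from communication with the medical team, and from the participant directly". No ranking or conflict rule follows. The same section makes pneumonia a secondary outcome: "Secondary study outcomes are incidence of pneumonia, maximum mouth pressures, and peak expiratory cough flow of reflex cough at day 29".
- **Study design** says who does the work: "One investigator conducts all study procedures, including screening for eligibility, gaining consent, conducting study assessments, and introducing and assisting with the intervention".
- **Randomization, blinding, and treatment allocation** says of that person, once the envelope is opened: "Thereafter, the investigator is aware of the participant’s group allocation". Of everyone else it says: "Participants, caregivers, and healthcare professionals are unaware of group allocation throughout the study period".
- **Statistical analysis** makes pneumonia an inferential comparison: "Fisher Exact test will be used to compare the incidence of pneumonia from baseline through week 4 between the three study groups". A Benjamini-Hochberg adjustment applies.

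The **Weaknesses** section confirms that the method was chosen deliberately: "it was decided to take a pragmatic approach and observe clinical and self-reported information on swallowing function and pneumonia". It mentions radiograph- and blood-based criteria as a possible alternative. It lists the unblinded investigator as a further, separate limitation.

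**The concern.** A documented diagnosis by the treating clinicians is a blinded determination. The plan has this source but does not let it settle the outcome: it sits beside conversations with the team and the participant's account. If a participant reports a chest infection that the notes do not show, or a clinician voices a suspicion that was never recorded, someone must decide whether it counts. On the article's description that is the investigator who knows the arm and assists with the training.

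The same applies to timing. Entry is allowed up to two weeks after stroke, and the comparison runs from baseline. The article does not say whether an episode already present at baseline counts.

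Reducing pneumonia is the clinical purpose of the research, and the Aims section asks for the size of the effect on it to inform a larger trial. If classification depends even slightly on knowledge of the arm, that estimate is biased by an amount the reader cannot recover.

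**Working it through.** **1. Who reconciles the sources.** Study parameters is written in the passive and names nobody. Study design assigns all study procedures to one investigator. The blinding section makes that investigator aware of allocation from the baseline session on. Together these leave no one else in the article to combine the sources. This is an inference from three sections, not a sentence in any of them.

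**2. Which sources are blind.** Records and team come from healthcare professionals, who are blind. Participants are blind too. All three inputs are therefore blind; what is unblinded is the asking, weighing and combining.

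**3. Is this only condensation in the article?** For swallow safety, the same section gives an explicit rule tied to routine clinical instructions. Pneumonia, which is tested inferentially, gets a list of sources and no rule.

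**4. Size of one decision.** Inputs: 20 completers per group, or 30 per group if all 90 are recruited (Sample size); rates of 15% in control and 7.5% in each training group (Weaknesses: "it could be assumed that both intervention groups would show a reduction in pneumonia rates from 15% to 7.5% compared with the control group").

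- One event is 1/20 = 5.0 points or 1/30 = 3.3 points of an arm's rate.
- Expected events at 20 per arm: 20 × 0.15 = 3.0 and 20 × 0.075 = 1.5 in each training arm.
- Expected events at 30 per arm: 4.5, 2.25 and 2.25.
- The 7.5-point difference is 1.5 events in an arm of 20 or 2.25 in an arm of 30.

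**5. Effect on the planned test.** I used the exact Fisher (Freeman-Halton) test on the 3 × 2 table, with events given as sham/inspiratory/expiratory. The p-value sums the probabilities of all tables with the same total that are no more likely than the one observed. For 4/0/0 at 20 per arm:

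p = 3 × C(20,4)/C(60,4) = 3 × 4,845/487,635 = 0.030.

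| Per arm | From | p | To | p | Decisions changed |
|---|---|---|---|---|---|
| 20 | 3/1/1 | 0.60 | 4/0/0 | 0.030 | 3 |
| 20 | 3/1/2 | 0.86 | 4/0/0 | 0.030 | 4 |
| 30 | 5/2/2 | 0.49 | 5/0/1 | 0.044 | 3 |
| 30 | 4/2/2 | 0.72 | 4/0/0 | 0.032 | 4 |
| 20 | 4/0/0 | 0.030 | 3/0/0 | 0.100 | 1 |
| 20 | 6/1/1 | 0.039 | 5/1/1 | 0.19 | 1 |
| 30 | 6/1/1 | 0.046 | 5/1/1 | 0.21 | 1 |

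The first four rows start from whole-number counts near the article's own rates. They show the fewest changes, all favouring training, that bring p below 0.05. The last three rows show that one change can remove significance. All p-values are before the Benjamini-Hochberg adjustment.

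**6. Context.** Power of this test at the article's rates and the unadjusted 5% level is about 7% with 20 per arm and 12% with 30. The article's own pneumonia figure, about 180 per group, is not an input here.

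**The case against.** The strongest reply has five parts.

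*Both weaknesses are disclosed.* True, and this lowers the weight. But they are disclosed separately, and the stated reason, sparing participants additional procedures, does not apply to a counting rule that adds none.

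*The text does not say that the investigator decides, or that any one source is enough.* This stands. A reader might infer that a participant's word alone makes a case. The article joins the sources with a plain conjunction and neither states nor excludes that. The point is the absent rule.

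*The blinded source is already used, and participants are blind as well.* This stands too. It would be wrong to say that the plan ignores its blinded clinicians or that self-report is itself an unblinded measure. What remains is the handling of discordant reports, and the article gives no indication of how often they occur.

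*The result is not that easily tipped.* A reader might infer that one decision in each direction creates significance. Pooling the training arms, 5/20 versus 3/40 (p = 0.103) does become 6/20 versus 2/40 (p = 0.013). But that starts from 25% versus 7.5% and is not the planned test. From the article's rates on the three-group test, one swap takes 3/1/2 to 4/1/1 (p = 0.86 to 0.34) at 20 per arm, and 5/2/2 to 6/1/2 (p = 0.49 to 0.14) at 30. Neither reaches 0.05. The fragility to a single event belongs to any small count and would persist under a better rule.

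*Definitions and baseline handling may sit in the full protocol or in Additional file 1, which is not shown.* Possibly. The baseline question in particular rests on silence, so I treat it as part of the remedy and not as a fault in its own right. The choice of unranked sources, however, is stated and defended in the article.

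**Conclusion.** The point holds in a limited form. The plan leaves a tested secondary outcome open to reconciliation by someone who knows the allocation, although a blinded diagnosis is available and could settle it. Each decision is worth 3.3 to 5.0 percentage points in an arm, and about three decisions in one direction can create nominal significance from counts near the article's rates.

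This assumes that the single investigator does the reconciling, that some reports are discordant, and that the illustrative 15% and 7.5% are roughly right. It does not show that bias occurs or that it would favour training: the direction is a risk, not a finding. With power of about 7% to 12%, the significance test on pneumonia will say little under either rule. The main loss is in the estimate passed on to a larger trial. The primary outcome, voluntary cough flow, is untouched by this point. The change is worth making because it costs little, not because the trial depends on it.

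**What to change.** For the week-4 comparison:

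1. Count a pneumonia diagnosis documented by the blinded treating clinicians, in a hospital or primary-care record, with recorded onset after randomisation.
2. Let participant or verbal reports trigger a check of the record, without counting on their own.
3. Flag episodes already documented at baseline, and count such a participant only if a new episode is recorded.
4. Report self-report-only episodes separately by arm, with a sensitivity analysis that includes them.

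The article describes recruitment as still under way and accepts revisions to the analysis plan, so the rule can be fixed now and applied to records already held.

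The cost is one rule on the case report form and some record requests, with no new tests. Because participants may be discharged home or transferred, a few undocumented community episodes may be lost, and that loss is not guaranteed to be equal across arms. The separate tabulation and sensitivity analysis are there to show whether it matters.

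### An investigator who knows the arm runs cough efforts with no stated limit and the five highest are analysed, so unequal effort counts between arms could bias the primary outcome

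*Protocol article*

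**What the plan says.** The Study parameters section of the protocol article fixes the endpoint: "Peak expiratory cough flow (PECF) of voluntary cough at the end of the intervention period (day 29) is taken as the primary study outcome". In the voluntary cough test, "participants make repeated maximal cough efforts into a tight-fitting face mask, until five coughs of similar PECF are recorded". The analysed parameters are then "derived for the five voluntary and five reflex coughs with the highest peak expiratory flow rates". The section gives no tolerance for similarity and no upper limit on efforts.

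The Study design section states who does the work: "One investigator conducts all study procedures, including screening for eligibility, gaining consent, conducting study assessments, and introducing and assisting with the intervention". The Randomization, blinding, and treatment allocation section states when the arm becomes known: "the investigator opens the respective envelope after informed consent has been gained and immediately before conducting the study baseline session". It continues: "Thereafter, the investigator is aware of the participant’s group allocation".

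The Weaknesses section concedes the general point: "A further limitation to the study is the lack of investigator blinding". It does not mention the cough test or a safeguard for it. In the Statistical analysis section, the covariates listed for the day-29 ANCOVA include neither the number of efforts nor baseline PECF. Baseline values do enter one of the four missing-data approaches, which substitutes them for missing day-29 values.

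**The concern.** PECF depends on effort, and its value here also depends on how many efforts are made. Taking the five highest of a larger set gives a higher result by selection alone. The person who decides when five coughs are alike enough to stop knows the arm. A stricter reading of similarity in one arm means more efforts there and a higher recorded PECF with no change in cough.

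What is at stake is mainly the estimate. The first objective under Aims and objectives is the magnitude of effect, which is meant to inform a larger trial. The baseline session is exposed too, because the envelope is opened before it.

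**Working it through.** **Planning figure, as a yardstick.** The Sample size section uses SD 50, difference 50 L/min, 80% power and a 5% level (taken as two-sided). n = 2 × (1.960 + 0.842)² × (50/50)² = 15.7, so 16 per group, as stated.

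**Step 1: selection effect for a fixed count.** Simulate k independent normal efforts with constant true cough (400,000 sets per k) and average the five highest. Excess over the true mean, in within-session SDs:

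| k | 5 | 8 | 10 | 12 | 15 | 20 |
|---|---|---|---|---|---|---|
| mean of five highest | 0.00 | 0.551 | 0.738 | 0.877 | 1.03 | 1.22 |

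**Step 2: convert to L/min.** The article gives no within-session SD and no effort counts. Assume an SD of 30 (range 20 to 50) and, for illustration, 12 efforts in one arm against 8 in another.
- SD 20: (0.877 − 0.551) × 20 = 6.5 L/min
- SD 30: 0.326 × 30 = 9.8 L/min
- SD 50: 0.326 × 50 = 16.3 L/min

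Against the initial 50 L/min these are 13%, 20% and 33%.

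The article does not say how the five values are summarised. If the single highest were used, the excess is 1.425 (k = 8) and 1.628 (k = 12), so the shift at SD 30 is 0.203 × 30 = 6.1 L/min.

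**Step 3: add the stopping rule.** Step 1 ignores the similarity rule, so simulate it. Assumptions: true PECF 300 L/min, within-session SD 30, stop once any five efforts agree within the tolerance, then average the five highest.

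| tolerance | mean efforts | upward shift (L/min) |
|---|---|---|
| 20% | 5.7 | 6.7 |
| 10% | 8.2 | 16.6 |
| 5% | 12.7 | 26.3 |

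The rule limits the effect but does not remove it. Reading similarity as 10% in one arm and 20% in another gives 16.6 − 6.7 = 9.9 L/min. If the same tolerance is applied in every arm and within-session variability is equal, the shift cancels.

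**Step 4: effect on the test.** With 20 per group, the standard error of a pairwise difference is SD × √(2/20): 31.6 L/min at group SD 100 and 79.1 at 250. For a 9.8 L/min shift the ratios are 0.31 and 0.12. With no true effect, a nominal two-sided 5% test rejects in 1 − Φ(1.96 − ratio) + Φ(−1.96 − ratio): about 6.1% and 5.2%. A wider contrast of 5 against 10 efforts, over within-session SDs of 20 to 50, gives about 8% to 22% at group SD 100 and 5% to 8% at 250.

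**The case against.** The strongest reply is that the two rules do not conflict. One says when to stop and the other says which traces to use. If similarity means a plateau of maximal efforts, the five alike and the five highest are largely the same coughs. That is right, and a reader who infers a contradiction goes further than the text. But the plateau reading does not remove the dependence. If the five highest must agree, the same simulation gives shifts of 8.1 L/min at a 20% tolerance and 29.2 at 10%.

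A second reply is that a tolerance, a cap and scripted encouragement are operating details that a condensed article leaves to the full protocol. This stands for those details, so their absence is not the finding. The finding rests on what is stated: the envelope opened before baseline, stopping on a judgement, selection of the highest, and one investigator who knows the arm.

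Third, the observed group SDs of about 100 to 250 L/min dwarf a 10 L/min shift. That is fair for the test. It does not make the estimate unbiased.

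Stronger readings are tempting and lack support:
- A reader might infer that the outcome has been distorted. Nothing shows that effort counts differed by arm.
- A reader might infer that the investigator coaches efforts. The article says only that this person conducts the assessments.
- A reader might infer that no analysis could repair the bias. Cough-flow traces are recorded, so if all efforts are kept they can be counted and re-analysed.

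**Conclusion.** The point holds as a conditional risk. The procedure as stated lets the primary outcome rise with the number of efforts, and the person controlling that number knows the arm. Bias between arms follows only if counts, or the reading of similarity, differ by arm. The illustrative size is about 10 L/min (6 to 16) for 12 against 8 efforts. It rests on an assumed within-session SD, assumed counts, and independent normal efforts without fatigue or learning. At the observed group SDs the effect on type I error is small for that contrast, and larger only for wide contrasts at the low end of the SD range. The bias in the estimated effect remains. The admission about blinding covers the general weakness but not this step. The procedure should be changed, though the risk does not invalidate the trial.

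**What to change.** 1. Open the envelope after the baseline cough and mouth-pressure tests and before training is taught. This protects baseline values, and so the baseline-substitution analysis. It does not protect the day-29 measurement.
2. Use the same set number of recorded maximal efforts for every participant and visit, and log the count.
3. Let software pick the five highest from files coded so that arm and visit are hidden.
4. Report the number of efforts by arm. For participants already tested, add a sensitivity analysis on the first N recorded efforts where traces exist. With N = 5 no selection takes place.

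**Cost.** Procedure wording, file coding and a selection routine that reads both the on-site and the off-site recordings. No added staff or visits. Some participants will not reach five similar coughs within the set number and should be flagged. At least 40 had completed by the sample-size review, so the procedure would change part-way; randomization in blocks of 12 keeps this roughly balanced across arms. Unequal encouragement by a tester who knows the arm is not fully removed.
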